#### Eligibility Criteria (Table 3)

To be eligible for the trial, subjects must fulfill all the inclusion criteria and none of the exclusion criteria, as stated in Table 3.

**Table 3 metabolites-13-00182-t003:** Eligibility criteria. BMI: body mass index; GFR: glomerular filtration rate; ICD-11: International Classification of Diseases 11th Revision; MADRS: Montgomery–Åsberg Depression Rating Scale; NSAIDs: nonsteroidal anti-inflammatory drugs; PPIs: proton-pump inhibitors; TASR: Tool of Assessment of Suicide Risk; TSH: thyroid stimulating hormone.

Inclusion Criteria	Exclusion Criteria	Reasons for the Participant to Be Discontinued from the Study
1. Depressive disorders diagnosed according to the ICD-11; 2. Age between 18–70 years; 3. MADRS score > = 13; 4. Anti-depressant and anti-anxiety medications not changed within 3 weeks prior to the recruitment visit.	1. Pregnancy; 2. An infection/vaccination and/or treatment with antibiotics in the previous 4 weeks; 3. Supplementation with pro- or prebiotics in the previous 4 weeks; 4. Having a diagnosis of an autoimmune disease, being seriously immunocompromised, inflammatory bowel disease, cancer, IgE-dependent allergy, or severe kidney failure in the previous 4 weeks; 5. BMI > 35; 6. GFR < 30 mL/min/1.72 m^2^; 7. Unstable thyroid dysfunction (TSH < 0.27 or >4.2 µIU/mL) in the previous 4 weeks; 8. Psychiatric comorbidities (except specific personality disorder, additional specific anxiety disorder, and caffeine and nicotine addiction); 9. Regular treatment (more than 3 days a week) with PPIs, metformin, laxatives, systemic steroids, or NSAIDs in the previous 4 weeks; 10. Significant change in dietary pattern in the previous 4 weeks; 11. Significant change in daily physical activity or undertaking an extreme sports activity in the previous 4 weeks; 12. Significant change in dietary supplementation in the previous 4 weeks; 13. Significant change in smoking pattern in the previous 4 weeks; 14. High risk of suicide; 15. Is participating in, or has recently participated in, another research study involving an intervention that may alter the outcomes of interest for this study; 16. Any other condition or situation which, in the view of investigators, would affect the compliance or safety of the individual taking part.	1. Withdrawal of informed consent; 2. An infection/vaccination and/or treatment with antibiotics during the trial; 3. Consuming any probiotics other than those studied during the trial; 4. Lack of compliance with the probiotic supplementation; 5. Any change in the drug regimen during the study; 6. Exclusion criteria found after enrolment; 7. Any serious adverse event during the trial.

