## Abstract

This article aims to present the theoretical basis, methodology, and design of a clinical trial we will conduct. The study will be prospective, randomized, placebo-controlled, and double-blind. Each intervention period will last 8 weeks and the trial will be conducted on 100 patients in total, who will be randomly divided into two groups consisting of 50 patients each. We plan to investigate the impact of *Lactobacillus helveticus Rosell* and *Bifidobacterium longum Rosell* on the depressive, anxiety, and stress levels in patients with depressive disorders with possible comorbid anxiety. In addition to assessing the influence of probiotics on the clinical condition, we also plan to study the clinical and biochemical parameters of metabolic syndrome, which often coexists with depression. Both depressive and metabolic issues may have part of their etiopathology in common, e.g., inflammation, oxidative stress, and dysbiosis. This is why we will additionally investigate the parameters related to gut microbiota, inflammatory, and oxidative statuses. Thus, the primary endpoint of the study will be the change in depression score measured with the Montgomery–Åsberg Depression Rating Scale. The secondary endpoints will include changes in anxiety and stress levels, as well as metabolic, inflammation, and oxidative stress parameters.

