#### Sample Size Calculation

As for the primary outcome of the study, namely, the MADRS score, we will use a standard deviation of 5.15 and a difference in the mean of 2.9 (M1 = 20.0, M2 = 17.1). We based our assumptions regarding the mean and standard deviation of MADRS in a depressed population on a study by Dijkstra et al. [49]. A difference in the MADRS of 2.2 points or higher seems clinically relevant (Cohen’s D has a value of 0.4, while a value of 0.4 or higher is widely considered to be associated with a clinically relevant effect size). Using an online tool (https://www.stat.ubc.ca/~rollin/stats/ssize/n2.html, accessed on 2 December 2022), we calculated the required sample size (assuming that both groups taking part in the study are the same size). The total sample size for this study should be around 100 (M1 = 20.0, M2 = 17.1, SD = 5.15, alpha = 0.05, power = 80%).

More details of sample size calculations for different secondary outcome measures are described in Appendix A.

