### 3.2. Design

The patients from the two clinical groups will undergo pharmacological and psychological treatment in compliance with the procedures of the clinic. It is worth mentioning that the researchers will at no stage interfere in the treatment process.

The patients will be recruited in the Central Teaching Hospital (inpatient and outpatient clinics), Medical University of Lodz, Poland.

We plan to measure the following metabolic parameters: blood pressure (BP), weight, body mass index (BMI), and waist circumference (WC). Blood samples of each patient will be collected to determine serum CBC and measure the levels of C-reactive protein, HDL cholesterol, triglycerides, and fasting glucose. Microbiota function (as SCFA concentrations in feces) and composition will be assessed. The oxidative stress level in the blood will be assessed as the total antioxidant capacity (TAC) and the level of malondialdehyde (MDA) concentration in blood plasma.

The patients will be observed for twenty weeks and they will be administered probiotic supplements for the first eight weeks.

The study will consist of the following visits:

V0 “recruitment visit”: assessment of inclusion and exclusion criteria, giving informed consent, a full psychiatric and somatic examination, filling in a survey questionnaire (SQ), and filling in the MADRS scale;

V1 “randomisation visit” (within 5 days following V0): filling in the DASS and WHOQOL-BREF scales; measuring BP, WC, and BMI; blood and stool collection; and • t1-t3:3/8 monitoring using personal contact via phone or e-mail every two weeks; 

V2 “final visit” after 8 weeks following V1: filling in MADRS, DASS, and WHOQOL-BREF scales; measuring BP, WC, and BMI; and blood and stool collection; 

V3 “follow-up visit” after 12 weeks following V2: filling in the SQ, MADRS, DASS, and WHOQOL-BREF scales and measuring BP, WC, and BMI.

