Patients included in group II (PLC-D) will receive the same capsule daily, containing only the excipients (potato starch and maltodextrin) and the capsule shell. The color, smell, and taste of the placebo will not be different from those included in the probiotic capsule (manufacturer—Sanprobi Sp. z o. o., Sp. k., Szczecin, Poland). The pill boxes will be labeled the same way. We decided that the intervention period will last 8 weeks because the recent clinical trials using probiotics demonstrated that it is rational to supplement the probiotics for at least 6–8 weeks to reduce the depression scale score [61,62,63]. We will assess how compliance is with personal, telephone, or e-mail contact every 2 weeks according to the monitoring questionnaire (MQ). Participants will be asked to collect the blister packs to evaluate compliance after the study and to fill in a daily medication chart. Patients will be considered compliant if they consume > = 80% of the supplements.

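### Table 3 ends study participation, not only capsule intake, for events after randomisation such as any drug change, so the week-8 MADRS of those patients would not be collected

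*Protocol article*

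**What the plan says.** The third column of Table 3 (section 3.2, Eligibility Criteria) concerns discontinuation from the study, not from the capsules. Apart from withdrawal of consent, it lists:

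- infection, vaccination or antibiotics during the trial;
- use of other probiotics;
- "Lack of compliance with the probiotic supplementation";
- "Any change in the drug regimen during the study; 6. Exclusion criteria found after enrolment; 7. Any serious adverse event during the trial".

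Section 3.2 (Design) places pharmacological and psychological treatment under the clinic's procedures and says that "the researchers will at no stage interfere in the treatment process". Patients come from inpatient and outpatient clinics. MADRS is recorded at V0, at V2 (8 weeks after V1) and at V3 (12 weeks after V2).

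The Abstract says that "the primary endpoint of the study will be the change in depression score measured with the Montgomery–Åsberg Depression Rating Scale". The sample size section uses "a standard deviation of 5.15 and a difference in the mean of 2.9 (M1 = 20.0, M2 = 17.1") and arrives at around 100 in total. Section 3.1 enrols 100, 50 per arm.

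Section 3.3 describes compliance monitoring every two weeks. It adds: "Participants will be asked to collect the blister packs to evaluate compliance after the study". It counts a patient as compliant at 80% or more of the supplements.

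**The concern.** Every listed reason except withdrawal of consent is a removal under the protocol's own rule, and all of them arise or come to light after randomisation. A change of drug in a depressed patient under clinic care is plausibly linked to how the depression is going, which is what MADRS measures. A serious adverse event or poor compliance may be linked to it as well, or to the arm.

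If such a patient leaves the study before V2, there is no week-8 MADRS. The choice of analysis set can wait for an analysis plan. The collection of the outcome cannot, because an analysis as randomised would then have to replace missing scores by assumption, for patients who may well differ from the rest. Two things are at stake: power, because the number randomised equals the number calculated, and the protection that randomisation gives to the primary comparison.

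**Working it through.** **Inputs from the protocol.** Means 20.0 and 17.1 (difference 2.9), SD 5.15, alpha 0.05, power 80%, 50 per arm. Sidedness is not stated for MADRS. Two-sided is used because it reproduces the stated total, whereas one-sided gives 39 per arm. V2 is taken as the time of the primary comparison.

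**1. The plan's own figure.**
n per arm = 2 × (1.960 + 0.842)² × 5.15² / 2.9² = 49.5, so 50 per arm and 100 in total. This matches. At 50 per arm, SE = 5.15 × √(2/50) = 1.03, 2.9/1.03 = 2.816, and power = Φ(2.816 − 1.960) = 80.4%. A t-test calculation gives 79.6%. The arithmetic is right and leaves no reserve.

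**2. Loss unrelated to outcome.** The documents give no rate, so 10% to 30% is an assumed range. Power = Φ(2.9 / (5.15 × √(2/m)) − 1.960), with m evaluable per arm.

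| Loss | m per arm | Power | Total to randomise for 50 evaluable per arm |
|---|---|---|---|
| 0% | 50 | 80.4% | 100 |
| 10% | 45 | 76.2% | 112 |
| 20% | 40 | 71.2% | 126 |
| 30% | 35 | 65.4% | 144 |

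The last column is 2 × 50/(1 − loss), rounded up per arm.

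**3. Loss related to outcome (illustration).** Assume that a patient whose week-8 MADRS would exceed 20 is removed with probability p, by the same rule in both arms. The share above 20 is 50.0% on placebo and 28.7% on probiotic. The mean score of those above 20 is 24.11 and 23.22.

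- p = 0.5: 25.0% and 14.3% are removed. Means of those left: (20.0 − 0.250 × 24.11)/0.750 = 18.63 and (17.1 − 0.1433 × 23.22)/0.8567 = 16.08. Difference about 2.55. Simulated power about 63% to 65%.
- p = 0.3: 15.0% and 8.6% are removed. Means 19.27 and 16.52, difference 2.75. Simulated power about 72% to 73%.

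Removing 25% and 14% at random, with no link to outcome, gives about 70%. In the first case, therefore, most of the lost power comes from fewer patients and the rest from selection.

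With no true effect and the same removal rule in both arms, the expected difference stays at zero.

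**4. What retention would recover.** Keep everyone and let a drug change, under the p = 0.5 rule, lower MADRS by b points. Expected difference = 2.9 − b × (0.250 − 0.143).

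- b = 3: about 2.58, simulated power about 76% to 77%.
- b = 5: about 2.37, simulated power about 73%.

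Both the removal rule and b are assumptions.

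**The case against.** The strongest reply is that the article names no analysis set and may leave this to an analysis plan that is not shown. That stands as far as analysis goes. A reader might infer from Table 3 that the trial plans a comparison of selected completers, but the documents do not say so. The point is confined to outcome data that the written rule would leave uncollected.

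Other limits also stand:

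- **Compliance.** Blister packs are evaluated after the study, when V2 and V3 scores already exist, so that check cannot lose them. A reader might infer that patients would then be excluded from the analysis once outcomes are known; Table 3 does not say this. Nor does it cite the 80% threshold, which comes from section 3.3. Only non-compliance found by the two-weekly monitoring could end participation before V2.
- **Window.** Patients are observed for 20 weeks, but events after V2 cannot remove a week-8 score. They affect V3 only.
- **Cause of drug changes.** It is tempting to say that these mostly reflect poor outcome. The documents do not show this: the rule covers any drug, including non-psychiatric ones and reductions after improvement, and entry requires antidepressant and anti-anxiety drugs unchanged for three weeks. A link to outcome is plausible, not established.
- **Bias.** Its direction is open. In the illustration the difference shrinks, which is conservative; arm-related removal could push either way.
- **Remedy.** Retention does not guarantee the planned 2.9 points and 80% power, as step 4 shows.

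**Conclusion.** The concern holds in this form: Table 3, as worded, ends participation for randomised patients on grounds that can be related to outcome, no text keeps them in follow-up, and their week-8 MADRS could not be recovered later. It should be changed before the data are collected.

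Only the lack of reserve follows directly from the protocol's figures. The power figures of 76% to 65% rest on assumed losses of 10% to 30%. The 2.5 to 2.8 points and 63% to 73% rest on an assumed removal rule. Neither set is a forecast, and the documents do not support a statement that the trial's result will be biased in a given direction.

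**What to change.** 1. In Table 3, separate discontinuation of the study product from discontinuation of study follow-up, and reconcile the list with section 3.2, which leaves treatment to the clinic. What happens to the capsules after each event remains a clinical judgement, and no rule is proposed here.
2. Unless consent is withdrawn, collect MADRS, DASS and WHOQOL-BREF at V2 and V3 for every randomised patient, and record the date and type of each event.
3. State that the primary analysis takes all randomised patients in their allocated arm. Use the compliant, no-drug-change set only as a sensitivity analysis.

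**Cost.** Protocol wording and a few more completed visits, since V2 and V3 already exist. The estimate will then include the effect of drug changes, so part, not necessarily all, of the planned difference and power is recovered: about 2.4 to 2.6 points and 73% to 77% under the assumptions of step 4.

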### 3.3. Interventions

At the beginning (V0), the patients will be asked to perform routine physical activity and not to modify their diet during the study. Patients included in group I (PRO-D) will receive one capsule daily containing a probiotic mixture at a daily dose of 3 × 10^9^ colony-forming units (CFU). The probiotic will be composed of two bacteria strains (*Lactobacillus helveticus Rosell^®^-52* and *Bifidobacterium longum Rosell^®^-175*), excipients (potato starch and magnesium stearate), and the capsule shell (made of hydroxypropylmethylcellulose). It will be ordered directly from the manufacturer (Sanprobi Stress^®^, Sanprobi Sp. z o. o., Sp. k., Szczecin, Poland). In our study protocol, we decided to use the combination of these two strains because both strains were studied in experimental and animal models and were found to improve emotional behavior in animals [50,51,52]. Clinical studies with healthy subjects and depressed patients showed inconclusive results [50,53,54,55,56]. We created a summative table with the list of the recent clinical trials with the efficacy of *Bifidobacterium longum* and *Lactobacillus helveticus* toward depressive, anxiety, and stress symptoms that could give the rationale for the combination of these two strains (Table 4). Interestingly, these two strains seem to also have specific effects on pro-inflammatory cytokine synthesis by reducing the level of pro-inflammatory cytokines, such as IL-1β, IL-6, and TNF-α, which may aid their antidepressant effect [57,58]. Moreover, recent study results suggested that Bifidobacterium species (spp.) positively correlated with both improved insulin resistance and obesity, and this might be associated with metabolic syndrome [59,60].

Patients included in group II (PLC-D) will receive the same capsule daily, containing only the excipients (potato starch and maltodextrin) and the capsule shell. The color, smell, and taste of the placebo will not be different from those included in the probiotic capsule (manufacturer—Sanprobi Sp. z o. o., Sp. k., Szczecin, Poland). The pill boxes will be labeled the same way. We decided that the intervention period will last 8 weeks because the recent clinical trials using probiotics demonstrated that it is rational to supplement the probiotics for at least 6–8 weeks to reduce the depression scale score [61,62,63]. We will assess how compliance is with personal, telephone, or e-mail contact every 2 weeks according to the monitoring questionnaire (MQ). Participants will be asked to collect the blister packs to evaluate compliance after the study and to fill in a daily medication chart. Patients will be considered compliant if they consume > = 80% of the supplements.

## 4. Discussion

Anxiety and depressive symptoms frequently co-occur. This fact may result in worsened functioning, a poorer prognosis, and a more severe and more chronic course of depressive disorders [64]. Unfortunately, although many joint studies were conducted, the common etiology of anxiety and depressive symptoms is still partly unclear. 

Consideration of the clinical picture is essential, as it allows for the identification of specific biomarkers and elucidation of the pathophysiological processes underlying the co-occurrence of depression and anxiety. In clinical practice, patients with such a clinical manifestation are often a major therapeutic challenge, as they less frequently respond to standard antidepressant treatment [65]. Recent studies, including meta-analytical summaries, emphasized the beneficial role of probiotic supplementation in reducing depressive symptoms when administered as an add-on [66]. Moreover, there is some evidence of the efficacy of probiotics toward symptoms of anxiety and stress [32,33,34]. Additionally, studies on new therapies confirmed that some of the strains of probiotics can also improve the clinical and laboratory components of metabolic syndrome and decrease the level of inflammation and oxidative imbalance [67]. Therefore, metabolic, inflammatory, or oxidative parameters may potentially serve as biomarkers of the therapeutic efficacy of probiotics toward depression with/without anxiety and stress features.

Clearly, our study protocol has both strengths and limitations. First of all, we decided to use the most recent classifications, i.e., ICD-11, in our study protocol. According to the ICD-11, depressive disorders include single-episode or recurrent depressive disorder, mixed depressive and anxiety disorder (MDAD), and dysthymia [68]. The distinction of depression with comorbid anxiety symptoms (“anxious depression”) underlying its clinical significance has an impact on a patient’s everyday functioning and quality of life [28]. Moreover, it is connected with its importance in primary care settings and because of evidence of its overlap with mood symptomatology [69]. Few studies investigated potential new treatment options for patients with MDAD and there is a huge need in the field. Therefore, we decided to include the whole category of depressive disorders as the first stage of the eligibility screen in our study. On the other hand, the study population will not be completely homogenous, as it will include both the category of mixed depressive and anxiety disorder (MDAD) and the category of major depressive disorder (MDD). 

It is well known that many factors that influence our microbiome, such as diet, treatment with antibiotics, metformin, proton pump inhibitors (IPP), viral or bacterial infections, vaccinations, air pollution, and cigarette smoking [70,71,72,73]. Obviously, we included the factors that may influence the microbiota changes in our microbiome in our original questionnaires, such as the survey questionnaire (SQ) at the beginning of the protocol and in the monitoring process every two weeks according to the monitoring questionnaire (MQ). However, we are not able to control for some factors, such as stress level, air pollution, or genetics.

Another limitation can be an insufficiently large patient population; the study will be conducted on 100 patients in total. Although the sample size in our study enables us to detect statistical significance, the authors are aware that it might not be enough for achieving clinical significance. In the case of research on microbiota influencing depressive symptoms, the reduction in depressive symptoms according to various scales is usually by a small number of points [56,74,75]. Moreover, a smaller sample size might in some cases fail to reject a null hypothesis. Therefore, further studies should be carried out. On the other hand, the calculated sample size seems similar to those from other studies regarding the effects of microbiota in psychiatric conditions [53,54,55].

In recent years, there has been a strong case for implementing a holistic approach to depression and recognizing it as a systemic disorder. The theory regarding the gut microbiome’s influence on the etiopathogenesis of depressive disorders is consistent with this approach [29,30,31,32], which confirms that probiotic supplementation may reduce depressive and anxiety symptoms. However, the number of such studies is still insufficient and their results are inconclusive. Studies on clinical populations are needed, as most interventions were conducted on healthy individuals. According to the most recent knowledge, probiotic supplementation may play an important role in modifying metabolic parameters [35] and favorably affecting inflammatory and oxidative stress parameters [37]. Our long-term scientific goals include understanding the relationship between the gut microbiota and anxiety and depressive symptoms, identifying a group of patients in whom probiotic supplementation may be an important component of antidepressant treatment, and generating a broad spectrum of therapeutic options for use in the clinical management of anxiety and depressive disorders. 

